#### Physician-patient-appointment after completion of the eAEP and fAEP (three and twelve weeks after study inclusion, respectively)

After completion of the eAEP as well as fAEP, essential contents of the education programs will be reviewed together with the GP using a questionnaire based on the national asthma care guideline (see Additional file 3 for further details). This final appointment is of high importance in order to verify the acquired knowledge of the patients. Therefore, an employee of the Institute of General Practice and Health Services Research at the Technical University of Munich will contact the patient by phone to ensure that the GP appointment is attended.

#### Follow-up at three (t_*2*_) and six months (t_*3*_)

After three and six months, the sustainability of the acquired asthma knowledge will be tested. For this purpose, patients receive a questionnaire by mail including the AKT, ACT and API as well as questions on the attitude towards asthma medication. Moreover, patients from general practices of the intervention group will be asked whether they have attended a fAEP in addition to the eAEP. Additionally, patients will answer questions regarding emergency treatments over the past six months at the six-month follow-up.

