### Aims and Outcomes

This cluster randomized controlled trial (cRCT) aims to investigate the effectiveness of the eAEP compared to usual care in terms of 1) asthma knowledge, 2) asthma control, and 3) emergency treatments including the following endpoints:Baseline-adjusted difference in the number of correctly answered questions in the AKT [8] between intervention and control groupsprimary endpoint: after the eAEP (two weeks after study inclusion) and fAEP (twelve weeks after study inclusion), respectively.secondary endpoint: three months after the eAEP (three months after study inclusion) and fAEP (six months after study inclusion), respectively.secondary endpoint: at the end of the study (six-month follow-up).

Further secondary endpoints include:2)Baseline-adjusted difference in the total sum score obtained in the asthma control test (ACT) [9] between intervention and control groupsthree months after the eAEP (three months after study inclusion) and fAEP (six months after study inclusion), respectively.at the end of the study (six-month follow-up).3)Difference in frequency of emergency treatments (inpatient and outpatient treatments of asthma) between intervention and control groups at six months.

This trial further examines the relation between asthma knowledge and 4) patient autonomy as well as 5) attitudes towards asthma medication including the following endpoints:4)Correlation between the total sum score achieved in the autonomy preference index (API) [10] at the time point baseline assessment and the change in correctly answered questions in the AKT after the eAEP and fAEP, respectively.5)Correlation between the total sum score obtained in the questionnaire on attitudes towards asthma medication at the time point baseline assessment and the change in correctly answered questions in the AKT after the eAEP and fAEP, respectively.

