All patients with asthma will be informed about the study and informed consent will be obtained. Patients from general practices in the intervention group will receive free access to the eAEP and will be asked to complete the eAEP within the following two weeks. Patients from general practices in the control group will receive usual care including a referral to a practice of pulmonology or a certified general practice for structured fAEP. Patients will be required to attend the fAEP within twelve weeks. As part of the baseline assessment, patients will complete a questionnaire including questions on their asthma characteristics, current medication and emergency treatments within the past six months. In addition, a structured questionnaire including the AKT, ACT and API as well as questions on patients’ attitude towards asthma medication will be handed out (further details on the questionnaires are depicted in the section ‘Measurements’). Furthermore, current lung function parameters will be extracted from patient chart or spirometry will be performed to assess lung function in terms of FEV_1_ and FEV_1_/FVC. Two weeks after study enrolment, all patients will receive the AKT by mail to complete the questionnaire again. After completion of the eAEP (three weeks after inclusion) or fAEP (twelve weeks after inclusion) patients will attend a follow-up consultation in the general practice in order to review the asthma knowledge gain as well as to discuss any open issues. In order to ensure adherence to the second appointment, all patients will be contacted via phone by an employee of the Institute of General Practice and Health Services Research at the Technical University of Munich. As part of a follow-up, patients in both groups will be contacted again by mail after three as well as six months and asked to complete a questionnaire comprising the AKT, ACT, API as well as questions on the attitude towards asthma medication. In addition, at the six-month follow-up, participants will be inquired to answer questions about emergency treatments. A detailed overview of the course of the present trial can be seen in Fig. 1.

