#### Emergency treatments

In order to record emergency treatments due to asthma attacks, patients will answer two questions. These include the number of inpatient as well as outpatient emergency treatments over the past six months.

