### Statistics

#### Sample size estimation

The power calculation is based on the results of the pilot study conducted in 2019 [7] using a two-sample t-test: An average difference of 22 points in the AKT (corresponding scale ranges from 0 to 54 points) was observed between baseline measurement and after completion of the eAEP (two weeks after study inclusion). A more conservative approach of an average difference of 20 points is applied for planning the current study. As the pilot study did not include a control group, an average asthma knowledge gain of 5 points was estimated for the control group of the present study. This estimation is based on the assumption, that about 25% of the patients in the control group will attend a fAEP and therefore achieve an average knowledge gain of maximum 20 points [3, 4]. The remaining 75% of the patients are expected to reach an average knowledge gain of 0 points. This results in 0.25 x 20 points + 0.75 x 0 points = 5 points. In order to include all available data in statistical analyses as well as to prevent an attrition bias, the intention-to-treat principle is applied in this study with an expected drop-out rate of 20%. Performing a worst-case-analysis [15], it is assumed that drop-out patients in the intervention group achieve an average knowledge gain of 0 points. Accordingly, an average asthma knowledge gain of 16 points is expected in the intervention group (0.80 x 20 points + 0.20 x 0 points). Considering a worst-case-analysis, the average asthma knowledge gain is assumed to double for drop-out patients in the control group resulting in an average knowledge gain of 6 points (0.80 x 5 points + 0.20 x 10 points). The sample size estimation is based on a standard deviation of 15. Using a two-sample t-test and a two-sided 5 % significance level, the number of patients per group is 36 to achieve a power of 80 %. Due to cluster randomization, the number of patients has to be increased by the design effect (DE). The sample size estimation of the current study is based on an intracluster correlation coefficient (ICC) of 0.10 [16], a mean cluster size of 5 and a resultant DE of 1.4 (calculation based on [13]). Regarding the primary outcome asthma knowledge gain, the number of patients required is therefore 100 (2 x 36 x 1.4 ≈ 100).

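### Emergency treatments are asked only once after baseline, over an undated six-month look-back, so late t3 forms lose the start of follow-up and patients lost after t2 contribute no follow-up events (minor)

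*Protocol article*

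**What the plan says.** Emergency treatments are the third aim of the trial. The endpoint is set out under Aims and Outcomes: "Difference in frequency of emergency treatments (inpatient and outpatient treatments of asthma) between intervention and control groups at six months". The Statistical analysis section reduces it to any event versus none and analyses it by GEE with group as covariate.

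The collection schedule is as follows.

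- **Baseline.** Study design lists "current medication and emergency treatments within the past six months" among the items asked.
- **t1 (two weeks).** "Two weeks after study enrolment, all patients will receive the AKT by mail to complete the questionnaire again". The intervention arm is also asked about internet use and fAEP attendance. No emergency item is listed.
- **t2 and t3 (three and six months).** "patients receive a questionnaire by mail including the AKT, ACT and API as well as questions on the attitude towards asthma medication". The emergency item is added for t3 only: "patients will answer questions regarding emergency treatments over the past six months at the six-month follow-up". Study design agrees: "at the six-month follow-up, participants will be inquired to answer questions about emergency treatments".
- **Recall period.** The Emergency treatments section describes the two questions: "These include the number of inpatient as well as outpatient emergency treatments over the past six months". Neither there nor elsewhere is the period tied to a date.

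Sample size estimation plans "with an expected drop-out rate of 20" per cent and does not say when drop-out occurs.

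**The concern.** Two features of this schedule weaken the endpoint.

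First, the window floats. It runs back from the day of completion, and the form is only mailed at six months. Any delay in answering therefore moves the window forward and drops the start of follow-up. For a yes/no endpoint, a patient whose only event falls in the dropped weeks changes from yes to no. A late event can also enter from beyond six months. If lateness differs between arms, which are not blinded at patient level, the error differs between arms too.

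Second, the only post-baseline question comes at the last contact. A patient who answers at three months and is then lost has been in contact with the study, yet contributes nothing to this endpoint. Information that an existing mailing could have held cannot be recovered later.

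**Working it through.** **The plan's own figure.** No event rate, power or sample size is given for emergency treatments. The only figure to reproduce is the total of 100, used below as the denominator. With a difference of 16 − 6 = 10 points, SD 15, two-sided 5% and 80% power, the t-test formula gives 36.3 per group (stated: 36). The design effect is 1 + (5 − 1) × 0.10 = 1.4, and 2 × 36 × 1.4 = 100.8, or about 100. The figure reproduces. Nothing below changes it.

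**Late forms.** Inputs: a follow-up of 26 weeks (six months), eAEP completion by week 2 (Study design), and a delay of L weeks, which is assumed because return times are not stated.

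Share of follow-up lost from the start = L / 26. Post-eAEP share lost, if the eAEP is finished at week 2 = max(0, L − 2) / 24.

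| Delay L (assumed) | Share of 26 weeks lost | Post-eAEP weeks lost, of 24 |
|---|---|---|
| 0 | 0% | 0 |
| 2 | 2/26 = 7.7% | 0 |
| 4 | 4/26 = 15.4% | 2 (8.3%) |
| 6 | 6/26 = 23.1% | 4 (16.7%) |

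The first two weeks lost are thus the eAEP fortnight itself. Post-eAEP time is lost only beyond about two weeks' delay, or sooner for a patient who finishes the eAEP earlier.

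**Patients lost after t2.** Inputs: 100 patients, 20% drop-out, and an assumed share s of that drop-out falling after t2. Patients affected = 100 × 0.20 × s.

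- s = 0: 0 patients
- s = 0.25: 5 patients
- s = 0.5: 10 patients
- s = 1: 20 patients

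**What missing t3 data do to the endpoint.** Assume 20% missing in each arm and the same observed risk p in both. If all missing patients in one arm had an event and none in the other did, the risk difference lies between 0.8p − (0.8p + 0.20) = −0.20 and (0.8p + 0.20) − 0.8p = +0.20, whatever p is.

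**What a t2 question would recover.** A yes at t2 settles the six-month endpoint. A no at t2 followed by loss leaves months three to six unknown. If a proportion q of the patients lost after t2 had reported an event, the unknown share falls from 0.20 to 0.20 − 0.20 × s × q. With s = 0.5 and q from 0.05 to 0.30 (both assumed), that is 0.195 to 0.170. With s = 1 it is 0.190 to 0.140. The gain is real but modest, and it depends on an event rate that the article does not give.

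**The case against.** The strongest reply is that the schedule is coherent. The endpoint is a six-month one, it is asked at six months over six months, and the baseline question uses the same recall length. That stands: an on-time form covers inclusion to t3. A reader might infer a contradiction between endpoint and measurement, but there is none.

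A second reply is that simply asking about the time since joining would be worse. Forms 2, 4 or 6 weeks late would then cover 28, 30 or 32 weeks, and longer exposure raises the chance of a yes. That also stands. It is the reason for printing both an opening and a closing date.

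Third, a t2 answer does not replace a six-month answer. This stands as shown in the working, so the 0 to 20 patients should not be read as complete outcomes regained.

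Fourth, missing data are already provided for, since analyses are to be run with and without worst-case imputation. This stands only in part. The values given, 0 and 10, are AKT points, and none is stated for a yes/no event. Imputation also fills a gap by assumption, which an observed answer would not.

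Fifth, the SPIRIT figure and the printed questions are not available here, and a form might carry a reference date. That is possible, but the text in Study design and in the follow-up section is consistent, and neither mentions one.

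A reader might also go further and infer that early deterioration is invisible to the study before month six, or that the weeks lost are those of greatest interest. The documents do not support either. Intervention patients see their GP at three weeks and controls at twelve, patients are telephoned, and the ACT goes to both arms at t2. Nor does the text single out the first weeks for this endpoint: the intervention arm has two weeks to complete the eAEP and controls have up to twelve weeks to attend the fAEP.

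**Conclusion.** The point holds as a minor weakness in how one secondary endpoint is measured. Two facts rest on the text alone: there is a single post-baseline assessment with no date anchor, and the t2 mailing omits the questions. The sizes rest on assumptions: 8%, 15% or 23% of follow-up lost for delays of 2, 4 or 6 weeks, and 0 to 20 of 100 patients without follow-up events, depending on when the 20% drop-out occurs. That 20% was set for the AKT calculation, and its use here is itself an assumption.

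It would be too strong to say that late forms generally miss the post-eAEP period. With completion at week 2 this begins only beyond about two weeks' delay. Nor is the point a safety finding. The primary analysis and the total of 100 are unaffected.

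**What to change.** - Add the two existing emergency questions to the t2 form, covering the inclusion date up to completion of t2.
- Word the t3 item with both dates pre-printed: from the inclusion date to the inclusion date plus six months. Every patient then has the same fixed window, and its length still matches the baseline recall.
- Define the binary endpoint as any event reported at t2 or t3 within that window.
- State how patients lost after t2 are handled. A yes at t2 settles the endpoint. A no counts as observed for months zero to three only and stays missing for months three to six, under the planned analyses with and without worst-case imputation.

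The cost is two questions on a form already mailed to both arms and two printed dates. An event may be reported on both forms, which cannot alter a yes/no endpoint.

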### Data Management and Monitoring

After informed consent is obtained and the data protection declaration is signed, the patient will be assigned a pseudonymized study ID. Further data and examination results are documented and stored under this ID. For instance, neither the name, nor the initials, nor the exact date of birth will appear in the identification number. The patient identification list remains at the Institute of General Practice and Health Services Research and will only be accessible to authorized study personnel. The data collection process as well as the study procedures will be supervised by a research associate.

### Risks

There are no immediate risks. However, it cannot be excluded that the content of the eAEP may be misunderstood in individual cases. Therefore, the follow-up review at the general practices will take place. As described in section ‘Measurements’, this second doctor’s appointment is of high importance in order to review the knowledge acquired by the patient. A reminder via phone will ensure that the patient attends this appointment.

### Statistics

#### Sample size estimation

The power calculation is based on the results of the pilot study conducted in 2019 [7] using a two-sample t-test: An average difference of 22 points in the AKT (corresponding scale ranges from 0 to 54 points) was observed between baseline measurement and after completion of the eAEP (two weeks after study inclusion). A more conservative approach of an average difference of 20 points is applied for planning the current study. As the pilot study did not include a control group, an average asthma knowledge gain of 5 points was estimated for the control group of the present study. This estimation is based on the assumption, that about 25% of the patients in the control group will attend a fAEP and therefore achieve an average knowledge gain of maximum 20 points [3, 4]. The remaining 75% of the patients are expected to reach an average knowledge gain of 0 points. This results in 0.25 x 20 points + 0.75 x 0 points = 5 points. In order to include all available data in statistical analyses as well as to prevent an attrition bias, the intention-to-treat principle is applied in this study with an expected drop-out rate of 20%. Performing a worst-case-analysis [15], it is assumed that drop-out patients in the intervention group achieve an average knowledge gain of 0 points. Accordingly, an average asthma knowledge gain of 16 points is expected in the intervention group (0.80 x 20 points + 0.20 x 0 points). Considering a worst-case-analysis, the average asthma knowledge gain is assumed to double for drop-out patients in the control group resulting in an average knowledge gain of 6 points (0.80 x 5 points + 0.20 x 10 points). The sample size estimation is based on a standard deviation of 15. Using a two-sample t-test and a two-sided 5 % significance level, the number of patients per group is 36 to achieve a power of 80 %. Due to cluster randomization, the number of patients has to be increased by the design effect (DE). The sample size estimation of the current study is based on an intracluster correlation coefficient (ICC) of 0.10 [16], a mean cluster size of 5 and a resultant DE of 1.4 (calculation based on [13]). Regarding the primary outcome asthma knowledge gain, the number of patients required is therefore 100 (2 x 36 x 1.4 ≈ 100).

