#### Control Group (usual care)

Patients from general practices in the control group will receive care as usual according to guideline recommendations. This encompasses either a referral to a pulmonary practice for structured fAEP or a structured fAEP in a certified general practice. Patients will be asked to attend the fAEP within twelve weeks. Furthermore, patients in the control group will also receive a peak flow meter and an asthma diary in advance.

Twelve weeks after study enrolment, patients in the control group will visit the general practice again to discuss remaining questions as well as to test patients’ asthma knowledge on the basis of the “physician-patient-appointment” questionnaire. At the end of the study, patients of the control group will also receive access to the eAEP.

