#### Statistical analysis

Descriptive statistics are used to describe the data included for the statistical analysis and are reported as the mean, standard deviation, median, quartile and ranges as well as absolute and relative frequencies. The primary endpoint is the asthma knowledge gain after the eAEP (two weeks after study inclusion) and fAEP (twelve weeks after study inclusion), respectively. A confirmatory hypothesis test for difference between intervention and control group is performed by a linear mixed-effects model at a two-sided 5% significance level. Based on the intention-to-treat principle, all patients will be included in analysis. The baseline value (number of correctly answered questions in the AKT at baseline), time since eAEP/fAEP, and group allocation (intervention or control group) will be used as fixed effects. Cluster effects of the general practices will be included in analyses as random intercepts. As previously mentioned, missing data for this variable will be imputed by performing a worst-case-analysis. Thereby, the average knowledge gain for drop-out patients is expected to be 0 points in the intervention group and 10 points in the control group. A comparison of the asthma knowledge gain between intervention and control group will also be made three months after completion of the eAEP (three months after study inclusion)/fAEP (six months after study inclusion) and at the end of the study (six-month follow-up). Similar calculations will be applied for the secondary outcome asthma control (difference in the achieved sum score of the ACT three months after completion of the eAEP/fAEP as well as at the six-month follow-up) (see Table 2). Emergency treatments as a secondary outcome will be considered binary in the analyses (0: No; 1: Yes, at least one emergency treatment). Due to the consideration of measurement repetition as well as data grouped in clusters, generalized estimating equations (GEE) will be applied. Group allocation is used as a covariate. Spearman or Pearson correlation coefficients will be calculated for the relation between 1) patients’ autonomy preference and asthma knowledge as well as between 2) patients’ attitude towards asthma medication and asthma knowledge. All analyses will be conducted exploratively with and without imputation in terms of a worst-case-analysis.

**Table 2 Tab2:** Overview of primary and secondary endpoints of the respective outcomes for linear mixed-effects models

			Time point (t)	

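### The stated 80% power makes no allowance for only 20 randomised practices: on the protocol's own inputs it is about 76% on 18 degrees of freedom, before any credit for baseline adjustment

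*Protocol article*

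**What the plan says.** All places are in the protocol article.

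- **Sample size estimation.** After worst-case imputation for 20% drop-out, "an average asthma knowledge gain of 16 points is expected in the intervention group". For controls the same step is described as "resulting in an average knowledge gain of 6 points". The planned difference is therefore 10 points, with an SD of 15. A two-sided 5% two-sample t-test is used, and "the number of patients per group is 36 to achieve a power of 80" per cent. With an ICC of 0.10 and a mean cluster size of 5, the design effect is 1.4 and "the number of patients required is therefore 100".
- **Study design; Recruitment and Randomization.** Twenty practices are randomised 1:1, so there are 10 per arm.
- **Statistical analysis.** The confirmatory test is "performed by a linear mixed-effects model at a two-sided 5% significance level". Baseline knowledge score, time since the education program and group are fixed effects. On clustering: "Cluster effects of the general practices will be included in analyses as random intercepts". No method for the degrees of freedom is named.
- **Control arm.** The control gain before imputation is 5 points, from a forecast that about 25% of controls attend the face-to-face program and gain 20 points while the rest gain none. On what controls are told, Study design says "Patients will be required to attend the fAEP within twelve weeks". The Control Group section says "Patients will be asked to attend the fAEP within twelve weeks".

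**The concern.** Group allocation varies only between practices. With 10 practices per arm, the information on the variability that matters for the group comparison comes from 20 practice means, which leaves 20 − 2 = 18 degrees of freedom. Multiplying an individual-level sample size by the design effect gets the standard error right. It still refers the test statistic to a distribution that treats that standard error as known almost exactly. With few clusters, this makes the calculated power too high.

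The 80% is the stated property of the one confirmatory test, so it should hold on the stated inputs or carry its condition.

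The control-arm assumption matters more for the size of the effect. The 10-point difference depends directly on how many controls attend. The protocol gives one forecast of attendance, shows no sensitivity to it, and describes the instruction to control patients in two ways.

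**Working it through.** **Inputs (Sample size estimation, Study design, Recruitment and Randomization).** Difference 16 − 6 = 10; SD 15; two-sided alpha 0.05; ICC 0.10; cluster size 5; 20 practices, 10 per arm; 100 patients, 50 per arm.

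**Step 1: reproduce the plan's figures.**
- Normal approximation: n per group = 2 × [15 × (1.960 + 0.842) / 10]² = 35.3, rounded up to 36.
- Design effect = 1 + (5 − 1) × 0.10 = 1.4.
- Total = 2 × 36 × 1.4 = 100.8, given as about 100.
- Power with 50 per arm and design effect 1.4 is 80.4% by normal approximation.

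The stated figures follow from the stated inputs by the standard method.

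**Step 2: allow for the number of practices.**
- Standard error = 15 × √(2 × 1.4 / 50) = 3.55. Practice means give the same: variance of a practice mean = 225 × (0.10 + 0.90/5) = 63, and √(2 × 63 / 10) = 3.55.
- Noncentrality = 10 / 3.55 = 2.82.
- Noncentral t power:

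| Degrees of freedom | Critical value | Power |
|---|---|---|
| 98 (patients) | 1.98 | 79.7% |
| 18 (practices) | 2.10 | 75.9% |

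A simulation of a t-test on practice means (200,000 runs) also gave 75.9%. The difference detectable with 80% power on 18 degrees of freedom is about 10.5 points.

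**Step 3: credit for the baseline covariate.** Let r be the correlation of baseline score with gain. It is not in the document, so it is an assumption here, as is an unchanged ICC after adjustment. The residual SD is 15 × √(1 − r²). Power on 18 degrees of freedom:

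| r (assumed) | Power |
|---|---|
| 0 | 75.9% |
| 0.2 | 77.6% |
| 0.3 | 79.7% |
| 0.31 | 80.0% |
| 0.4 | 82.8% |

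Reaching 80% needs a residual SD of 14.26, that is, baseline explaining 1 − (14.26/15)² = about 10% of the variance in gain.

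**Step 4: control attendance.** With attendance a, and drop-outs imputed at 0 points (intervention) and 10 points (control) as in Statistical analysis, the control mean is 0.8 × 20a + 0.2 × 10 and the difference is 16 minus that. Only the 25% is the protocol's; the other rates are assumptions.

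| Attendance | Control mean | Difference | Power, 18 df |
|---|---|---|---|
| 25% (protocol) | 6.0 | 10.0 | 75.9% |
| 35% (assumed) | 7.6 | 8.4 | 61% |
| 50% (assumed) | 10.0 | 6.0 | 36% |

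**The case against.** The strongest reply on power is that 75.9% belongs to an unadjusted comparison of practice means, which is not the planned test. The confirmatory model contains baseline score, and a correlation of about 0.31 with gain restores 80%. That is plausible. The Background reports a doubling of the score in the pilot study and the sample size section a gain of 22 points on a 0 to 54 scale, so patients who start high have limited room to gain. The protocol also names no degrees-of-freedom method, which may be left to the analysis plan. This stands as far as it goes, and it makes the shortfall conditional. However, the sample size section claims no credit for the covariate and states no correlation. A method giving close to 98 degrees of freedom would disregard that practices, not patients, are allocated.

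Two stronger readings are tempting, and the document supports neither.

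- A reader might infer an arithmetic error, because 36 per group gives 79.7% by the exact t-test (37 gives 80.8%) and 100.8 is rounded down. But 36 is correct by normal approximation, and the rounding is shown openly. Neither changes a decision.
- A reader might infer that the 25% attendance contradicts the requirement to attend. It does not: 25% is a forecast of uptake, and the Background says that few patients take part in such programs. An instruction and a forecast of compliance can differ. Nor does the text show that practices would run different comparators: both sections describe the same referral and the same twelve-week window. The firm textual conflict is only between the two wordings of the instruction.

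**Conclusion.** The point holds as an omitted small-cluster correction. On the protocol's inputs, and taking 18 degrees of freedom as the reference for a practice-level factor in a balanced design, power is about 76%, some 4 percentage points below the stated 80%. Equivalently, 80% applies to about 10.5 points instead of 10. Both figures are before baseline adjustment and assume equal practice sizes. It would be wrong to say that the design cannot reach 80%: whether it does depends on a baseline correlation that the document does not give.

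The two wordings of the control-arm instruction conflict and need reconciling. The attendance scenarios do not show that the stated power was miscalculated. They show that power is far more sensitive to the 25% forecast than to the degrees of freedom.

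**What to change.** 1. In Sample size estimation, either restate the power as about 76% on 18 degrees of freedom without covariate adjustment (or 80% for a difference of about 10.5 points), or keep 80% and state the baseline-to-gain correlation it relies on, about 0.3, labelled as an assumption.
2. Add a short table of power at other control attendance rates, for example 35% and 50%, under the stated imputation and labelled as assumptions.
3. Reconcile the instruction to control patients in Study design with that in the Control Group section, so that the document gives one description of it.

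The cost is wording only. No extra patients or practices are needed; the stated power becomes slightly less favourable or gains an explicit condition.
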